#### Randomization and rationale for stepped-wedge design

The 18 LGAs will be randomly allocated to the intervention, 4–5 LGAs per month for 12 months. All sites begin as part of the control condition and are block-randomized into four waves, with each wave beginning two months after the start of the prior wave and lasting for 6 months, followed by a 6-month follow-up period. All clusters will eventually receive the intervention, with outcomes measured every three months across all clusters. See Fig. 2for a schematic of the stepped-wedge cluster RCT design. Randomization will be conducted by the study statistician, who will not have direct contact with the LGAs. All LGAs will be informed of their assigned intervention wave before the first wave begins. Blinding was not implemented in this study, as all sites will eventually receive intervention, reflecting typical conditions in real-world settings. The stepped-wedge design was deemed acceptable and ethical by key program partners (NIMR and the Nigerian Ministry of Health) and study collaborators for logistical and pragmatic reasons, given the potential benefits of the intervention package (i.e., combined cervical cancer prevention strategies of vaccination and screening) and the equitable provision of the intervention to all sites [40].

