#### Sample size and power considerations

We performed an a priori power analysis to determine the sufficient sample size for the stepped-wedge cluster RCT design, where the unit of randomization is the geographic area (cluster). Thus, there are two important sample estimates: N, for the number of mother/daughter dyads and K, for the number of LGAs. Specifically, the N participants will be nested within the K clusters. This nesting will likely create dependency on the data. The degree of this dependency depends on the intraclass correlation coefficient (ICC). The required sample size is calculated for the primary outcomes of HPV vaccination uptake for daughters and HPV self-collection uptake for mothers. Assuming a total of 18 LGAs with 34 dyads per LGA (N1 = 18 × 34 = 612 for daughters and N2 = 18 × 34 = 612 for mothers, total N = N1 + N2 = 1224), four total intervention periods, 2-sided alpha = 0.05 and 80% power, we calculated the minimum detectable rate of the primary outcome uptake at follow-up (Table 3 below). We expect three possible baseline rates of 0.10, 0.15, and 0.20 and compute the minimum detectable differences between the baseline and follow-up rates (hence minimum detectable follow-up rates) for the two primary study outcomes, assuming three possible ICC values of 0.005, 0.01, and 0.05. As shown in Table 1, the minimally detectable follow-up rates are much less than expected of the follow-up 50–60% self-collection uptake rates [67–69] and 65% HPV vaccination [11]. Hence, we have sufficient power (> 80%) to detect the increases in HPV vaccination among girls and HPV self-collection among their mothers after the implementation of the final crowdsourced campaign with a total of 18 clusters with 34 dyads per cluster (Table 3). To account for the 15% attrition rate at 6 months follow-up, we increased the sample size to 704 for mothers and daughters (40 dyads for each cluster). The calculation was performed using the software PASS 2019 (Power Analysis and Sample Size Software (2019) with the formulas developed by Hussey et al. [70]

**Table 3 Tab3:** Power and sample size for stepped-wedge RCT^a^

Cluster size (total sample size)	Rate of primary outcome at baseline (HPV self-collection uptake for mothers, HPV vaccination for daughters)								
	0.10^a^			^a^0.15			^a^0.20		
	ICC			ICC			ICC		
	0.005	0.01	0.05	0.005	0.01	0.05	0.005	0.01	0.05

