### Statistical analysis

#### Data analysis

The primary analyses will examine rates of HPV self-collection (mothers) and single-dose vaccine receipt (daughters). Analyses will be performed separately for the mother sample and daughter samples. The main analyses will compare the rates of HPV self-collection (mothers) and vaccine uptake during the pre-and post-intervention periods. We will examine a hypothesis comparing the superiority of the intervention with pre-intervention periods using the stepped-wedge cluster randomized control design and account for any temporal changes in HPV vaccination or screening rates during the 6-month conduct of the trial. This analysis will be accomplished with generalized linear mixed models to account for the within-person factor – time (baseline, 3 months, and 6 months) and one primary between-person factor (randomization site dummy code as 0 = convention and 1 = intervention). The 3-level model is structured as observations nested within subjects within local government areas. Multilevel modeling software (SAS, version 9.4, PROC GLIMMIX with logit as link function) will be used to compute full information maximum likelihood (FIML) estimates of the model parameters. The model will include intervention status and time as fixed effects and site and individuals as random effects. The estimated intervention effects will be reported with 95% CIs and p values. Secondary analyses will explore linkage rates to clinical follow-up after positive HPV testing in pre-intervention and post-intervention periods.

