Adoption (daughters)	Uptake of HPV Vaccination among Daughters	The proportion of eligible girls with HPV vaccination receipt (one dose)	Baseline, 3 months, 6 months
Penetration (i.e. Levels of Institutionalization Scale)	Penetration Cronbach alpha = n/a	The extent to which components of the mother-daughter HPV campaigns are institutionalized within participating LGAs	Baseline, 3 months, 6 months
Implementation fidelity	Evidence that all core intervention components were delivered as intended and an assessment of intervention implementation concerning the study protocol consistency of implementation across the 18 local government areas	More specifically, fidelity will be assessed both quantitively and qualitatively using the following four dimensions: (1) Frequency, number of intervention-related interactions; (2) Duration: length of each component of the intervention; (3) Content: the knowledge or behavioural change the combined intervention seeks to deliver to the mother/daughter dyads; and (4) Coverage: the number of mother/daughter dyads who receive the intervention as intended over the number of participants who are enrolled	Baseline, 3 months, 6 months
Identification of barriers to HPV vaccination and/or screening	Open-ended semi-structured questionnaire	Qualitative research will examine barriers to vaccination/screening and reasons for failure to complete vaccination/screening	Baseline, 3 months, 6 months
General	Socio-demographic Characteristics	Six items included participants'age, sex, education level, place of residence, parent’s education level, family composition, and structure	Baseline, 3 months, 6 months and 12 months
Implementation leadership support	Measured using the Sustainment Measurement System Scale [73]. Items will be rated on a 5-point Likert scale ranging from 1 (not at all) to 5 (all the time), with lower scores indicating lower levels of agreement while higher scores indicating higher levels of agreement	Three-item subscale measuring the active engagement of leaders and/or program champions in project implementation and sustainment	Baseline, 3 months, 6 months and 12 months
Responsiveness to mother/daughter preferences and needs for HPV preventive campaigns		The three-item subscale measures the needs of the target population being served and their consistency and fit with norms and values	

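### The stated primary model uses none of the prognostic baseline variables the trial collects; adding a short pre-specified list would give a small gain in power and, if different dyads are enrolled under control and intervention, remove bias from measured case-mix shifts

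*Protocol article*

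**What the plan says.** The Data analysis section fixes the software, the link ("PROC GLIMMIX with logit as link function"), three levels of nesting and the terms: "The model will include intervention status and time as fixed effects and site and individuals as random effects". No baseline covariate is named for the primary analysis anywhere in the article. The sentence does not say that covariates are excluded.

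Table 4, in the section on implementation outcomes and process evaluation, lists socio-demographic data: "Six items included participants'age, sex, education level, place of residence", plus parental education and family composition. They are recorded at baseline and again at 3, 6 and 12 months.

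The section on randomization and the rationale for the design says "Blinding was not implemented in this study", and that every local government area (LGA) learns its wave before the first wave starts. The Methods section has the community health workers both recruit dyads and deliver the campaign.

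The article describes the source of control and intervention observations in two ways. The Data analysis section says the model will "account for the within-person factor – time (baseline, 3 months, and 6 months"), which is a repeated-measures cohort. The same sentence treats the intervention as "one primary between-person factor (randomization site dummy code as 0 = convention and 1 = intervention"), which suggests that each person is seen under one condition.

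**The concern.** Education and residence plausibly predict both vaccination and self-collection. A model that omits them gives up some power, and the data to include them are already being collected.

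The second issue is who is enrolled. Recruitment is open, runs through venues, schools, religious settings, referral and social media, and is done by staff who know when their LGA crosses over. If dyads are enrolled under both conditions, the mix of families can change at crossover. Such a change arises after randomization and follows the condition, so randomizing the wave order does not prevent it. The site term removes stable differences between LGAs, and the time term removes calendar trends that all LGAs share. Neither removes a change within an LGA that coincides with its own crossover. Any such change in a prognostic variable enters the effect estimate.

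**Working it through.** **1. Reproducing Table 3.** Inputs from the sample size section: 18 LGAs, 34 dyads each, "four total intervention periods, 2-sided alpha = 0.05 and 80% power", baseline rates 0.10, 0.15 and 0.20, ICC 0.005, 0.01 and 0.05. Assumed: waves of 4/5/4/5 LGAs, T = 5 periods and n = 7 dyads per LGA-period (34/5 = 6.8, rounded up). The Hussey–Hughes variance is

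Var = I·s·(s + Tτ²) / [(IU − W)s + (U² + ITU − TW − IV)τ²], with s = σ²/n.

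- U = 4×4 + 5×3 + 4×2 + 5×1 = 44
- W = 0² + 4² + 9² + 13² + 18² = 590
- V = 4×16 + 5×9 + 4×4 + 5×1 = 130
- IU − W = 792 − 590 = 202
- U² + ITU − TW − IV = 1936 + 3960 − 2950 − 2340 = 606

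Example: baseline 0.10, follow-up 0.235, ICC 0.05.
- σ² = (0.0900 + 0.1798)/2 = 0.1349; τ² = 0.05 × 0.1349/0.95 = 0.00710; s = 0.1349/7 = 0.01927
- Var = 18 × 0.01927 × (0.01927 + 0.03550) / (202 × 0.01927 + 606 × 0.00710) = 0.01900/8.195 = 0.00232, so SE = 0.0481
- Power = Φ(0.135/0.0481 − 1.96) = Φ(0.84) = 0.80, as printed.

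All nine printed rates come back within 0.002. Counting all 34 dyads in every period instead gives 0.153 to 0.159 at baseline 0.10, against the printed 0.216 to 0.235. So the power calculation fits about 7 dyads per LGA-period.

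**2. Gain on the rate scale.** The article gives no covariate R², so it is assumed. With 6.8 dyads per LGA-period and the within-cluster variance multiplied by (1 − R²), the minimum detectable rate is:

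| Baseline / ICC | R² = 0 | 5% | 10% | 20% |
|---|---|---|---|---|
| 0.10 / 0.01 | 0.224 | 0.221 | 0.217 | 0.210 |
| 0.20 / 0.05 | 0.363 | 0.359 | 0.355 | 0.346 |

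In these rows the gain is 0.3 to 1.7 percentage points. At the expected follow-up rates of 50% and 65%, power without covariates is already at least 0.998 for every baseline rate, at ICC 0.005 and 0.05.

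**3. Gain on the planned logit scale.** Illustrative simulation: 612 people, no clustering, one covariate.

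| Covariate log-OR per SD | Unadjusted log-OR (SE) | Ratio | Adjusted log-OR (SE) | Ratio |
|---|---|---|---|---|
| 0.3 | 0.886 (0.213) | 4.16 | 0.900 (0.215) | 4.19 |
| 0.6 | 0.846 (0.207) | 4.09 | 0.899 (0.214) | 4.20 |
| 1.0 | 0.779 (0.198) | 3.93 | 0.918 (0.216) | 4.25 |

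The SE rises with adjustment, but the estimate moves further from zero, so the ratio rises a little. Power here is near its ceiling (0.987 against 0.987 to 0.988). In a separate check with power away from the ceiling, the SE went from about 0.356 to 0.376 and power from about 0.72 to 0.74.

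**4. Bias if different dyads are enrolled under each condition.** To first order, bias on the rate scale ≈ shift × covariate log-odds × p(1 − p). Assumed: a 10-point shift in the educated share and a log-odds of 1.0 for education.
- No effect, p = 0.10: 0.10 × 1.0 × 0.09 = 0.9 points
- No effect, p = 0.20: 0.10 × 1.0 × 0.16 = 1.6 points
- Uptake rising from 0.20 to 0.44: mean p(1 − p) = (0.160 + 0.246)/2 = 0.203, so 2.0 points

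Simulated stepped-wedge trials (18 × 34 dyads, five periods, waves of 5/4/4/5, log-odds 1.0 for education, 0.7 for urban residence and 0.3 per SD of age, linear model with LGA and period effects) agree: +1.7 points when the true effect is zero and +1.9 points when it is 24 points. The adjusted estimates were essentially unbiased. A 15-point shift gave about +2.8 points. With no shift, the SD of the effect went from 0.0650 to 0.0630, a variance ratio of 0.94. The bias is 1.9/6.5 = 0.29 of one SD.

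**The case against.** **Covariates belong in the analysis plan.** A condensed article may leave them to a document that is not shown, and the model sentence lists what is included without excluding anything. An unadjusted primary model in a randomized trial is also legitimate. This stands in part: the omission is not an error. But the article chose to state the model's terms, and the stated model can be improved at almost no cost.

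**A cohort has no case-mix shift.** The repeated measures at baseline, 3 and 6 months, the individual random effect, the single baseline survey of 612 dyads and the 12-month follow-up all suggest that the same dyads contribute throughout. Fixed traits then cannot differ between conditions, apart from what the expected 15% attrition does. This stands under that reading. Pointing the other way are the between-person label, an outcome timed from each dyad's own enrolment, and the roughly 7 dyads per LGA-period behind Table 3. The article does not settle it.

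**The sizes are assumed and small.** This stands. The covariate effects and the shift are not in the article. The bias simulation is a linear stand-in without repeated measures, not the planned three-level logit model.

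**Adjustment does not cure selective recruitment.** This stands. If recruiters enrol more willing families after crossover, age, education and residence capture little of it. The adjusted estimate is unbiased in the simulation because only a measured variable was shifted.

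A reader might infer that the stated model makes the log-odds ratio less precise, or leaves the trial unprotected against confounding. The article supports neither: the SE of the log-odds ratio does not fall with adjustment, and randomized wave order, site and time terms already protect against much else.

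**Conclusion.** The point holds as a low-cost improvement. The stated primary model uses none of the prognostic baseline variables that Table 4 collects. Naming a few would raise power slightly: about 0.72 to 0.74 in one illustrative check, and 0.3 to 1.7 points in the minimum detectable rate for an assumed R² of 5 to 20%. Planned power at the expected uptake is ample without it.

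The stronger reason is conditional. If different dyads supply the control and intervention observations, a measured within-LGA shift at crossover biases the stated model. For a 10-point education shift the bias is about 1 to 2 percentage points, given an education log-odds of 1.0 and control uptake of 0.10 to 0.20. That is small beside an effect of the size the trial expects. If the same dyads supply both, this reason largely falls away. In either case unmeasured differences remain.

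Naming the covariates before results are seen also guards against selective adjustment later in an unblinded trial with 18 clusters.

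**What to change.** Change the model sentence so that the fixed effects are intervention status, time, and a short pre-specified set of baseline covariates: mother's age, daughter's age, mother's education and place of residence. Use baseline values only, since Table 4 records these items repeatedly and later values could follow the intervention. Add a simple rule for missing values, such as a missing category. Report the model without covariates as a sensitivity analysis.

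State in the same place whether dyads are enrolled under both conditions or whether the same dyads contribute to both, because the second benefit turns on this.

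The cost is a sentence or two and no new data. The downsides are a few extra parameters with 18 clusters and an odds ratio that is conditional on the covariates. For that reason, also report the effect as a standardised risk difference.

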### Study setting aims and approach

#### Setting

Nigeria’s population is estimated at over 200 million, of which 49.3% are female [50, 51]. The country has 36 states mapped into six geopolitical zones with a Federal Capital territory [50]. There are also 374 distinct ethnic groups and indigenous languages spoken throughout its 36 states and Federal Capital Territory [50]. Data from the most recent Demographic Health Survey (2018) estimates that the median age at first sexual intercourse among women is 17 years of age and first marriage at 19 years [52]. Nearly half of women aged 25–49 give birth for the first time before age 21, while 19% of teenage women aged 15–19 have begun childbearing [52]. The Literacy rate in Nigeria is 60% [53]. Also, 65% of women aged 15–49 are employed or self-employed [52], while the monthly minimum wage is 30,000 naira ($18.4) [54]. Although HPV vaccine coverage has increased with the nationwide rollout at 75% [55], it remains notably below the 90% target needed to eliminate cervical cancer as a public health concern. Additionally, despite recommendations for routine cervical cancer screening for women aged 30–49, cervical cancer screening coverage remains under 10% [56, 57]. HPV self-sampling, a potentially accessible method for increasing screening uptake, is also not yet widely implemented or routinely practiced in Nigeria. Organized cervical cancer screening programs are limited, particularly in community settings where most individuals receive healthcare. Our partnership with the Nigerian Institute for Medical Research is critical for enhancing the feasibility of the study. As the key research hub within the Nigerian Ministry of Health, NIMR is well-positioned to design and deliver the intervention across the 18 recruited local government areas within the six geopolitical zones of Nigeria (See Fig. 1).

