### Participants

Our stepped-wedge cluster-randomized trial will consist of two types of participants: 1) mother-daughter dyads recruited from 18 randomly selected LGAs across six geo-political zones in Nigeria with access to NIMR-affiliated clinical staff and 2) CHWs (one per LGA) and supervisors (one per LGA) implementing the intervention. Study eligibility criteria are described in Table 1.

**Table 1 Tab1:** Inclusion and exclusion criteria

Inclusion criteria (mother-daughter dyads)	• Both the mothers'/caregivers’ (between ages 30–49 years) and daughters'(Between 9 to 14 years) willingness to participate in the study• All participants must agree to informed consent in English or Pidgin English, Nigeria's second most common language.• Parental or guardian’s cell phone number for follow-up
Exclusion criteria (mother-daughter dyads)	• Inability to comply with the study protocol • Girls with recent vaccination for HPV or mothers recently screened for cervical cancer (within the last 5 years) • Illness, cognitive impairment, or threatening behaviour with acute risk to self or others

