#### Recruitment

We will enroll mother-daughter dyads in the 18 LGAS. Recruitment methods include in-person events and venue-based, participant referral, community, religious setting and school-based referrals, social media, and online referrals. First, mother-daughter dyads will be identified and recruited to participate in an upcoming Mother-Daughter Day event on HPV prevention methods. Second, those who agree to participate will receive reminder text messages before the event. Third, trained CHWs and supervisors will provide educational information and materials on cervical cancer control at the event.

Fourth, onsite services for HPV vaccination and self-collection kits will be offered to mother-daughter dyads, with girls receiving HPV vaccinations immediately in an onsite vaccination dedicated private space designated for the mother-daughter Day event. Mothers will receive instructions on self-collection in a private area, and their samples will be returned to the NIMR laboratory. Trained CHWs will provide the results of the samples, and those with positive results will be linked immediately to the supervisors for treatment and follow-up care, which we will track overtime. A baseline survey will be conducted among 612 mother/daughter dyads (*n* = 1,224 total) recruited in 18 LGAs (capped at 34 per area). We will define mothers as any female caregiver, including biological and surrogate mothers or close relatives who meet eligibility criteria. Eligibility criteria for mother-daughter dyads are outlined in Table 1. Trained community healthcare workers will approach and obtain consent from participants in a private space. Parental mobile phone numbers will be collected as tracking information for follow-up and retention.

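### Linkage to care after a positive HPV test is set out by pre- and post-intervention period, but pre-intervention positives will be few and self-selected, so the contrast cannot show an intervention effect on linkage

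*Protocol article*

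**What the plan says.** The protocol article, Data analysis, states that secondary analyses will "explore linkage rates to clinical follow-up after positive HPV testing in pre-intervention and post-intervention periods". The Outcomes section says only that linkage of women with positive results will be tracked. The Discussion lists linkage as a secondary outcome and ties its denominator to positive self-collection results.

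The steps that lead to that denominator and numerator are described as follows.

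- **Testing.** Under Recruitment, at the Mother-Daughter Day event, "onsite services for HPV vaccination and self-collection kits will be offered to mother-daughter dyads". Outcomes counts completion by receipt of the specimen at the study laboratory, and the Methods introduction has community health workers (CHWs) carry the samples there.
- **Linkage.** Also under Recruitment, CHWs give the results and "those with positive results will be linked immediately to the supervisors for treatment and follow-up care". The section on the implementation strategy bundle makes the training of these supervisors, who can treat mothers who test positive, part of the bundle.
- **Background.** The Setting section says that self-sampling "is also not yet widely implemented or routinely practiced in Nigeria" and that "cervical cancer screening coverage remains under 10" percent. Table 1 excludes "mothers recently screened for cervical cancer (within the last 5 years" before enrolment).
- **Planning rates.** The sample size section says: "We expect three possible baseline rates of 0.10, 0.15, and 0.20". It expects 50-60% self-collection at follow-up.

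**The concern.** A linkage rate needs women who have tested positive. In the post-intervention periods the campaign supplies them: it brings the kit, returns the result and makes the referral. In the pre-intervention periods the document describes nothing that does so. The plan thus sets a rate from a very small group, of unclear origin, beside a rate that the campaign largely generates.

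There is a second problem, which does not depend on numbers. Testing positive happens after randomisation and requires testing, which the intervention is designed to increase. Women who find a test for themselves under usual care may differ from women tested at a campaign event in motivation, symptoms and access to care, and each of these plausibly affects linkage. Randomisation of LGAs to waves does not balance the two sets of positives.

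At stake is what this secondary outcome can conclude. A difference between periods could be taken as an effect of the campaign on follow-up care when it reflects who was tested.

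**Working it through.** **The plan's own figure.** The document gives no expected number of positives and no power for linkage, so there is no linkage figure to reproduce. Table 3 (minimum detectable primary outcome rates) was reproduced to learn how mothers are spread over time. The Hussey-Hughes variance with 18 LGAs in waves of 5, 5, 4 and 4, five periods and 7 mothers per LGA-period (34/5 = 6.8, rounded up) matches all nine cells within 0.002; for example 0.218, 0.221 and 0.235 against the stated 0.216, 0.220 and 0.235. Other layouts come similarly close, so this one is not unique, but 34 mothers per LGA-period does not reproduce the table.

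**Inputs from the document.** 612 mothers in 18 LGAs; screening coverage under 10%; baseline self-collection 0.10 to 0.20; follow-up self-collection 50-60%; four waves, two months apart.

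**Assumptions, not in the document.** HPV positivity 10-25%. For route (a), coverage of 10% accumulates over 5 years, so at most 2% of mothers are screened per year, and each mother spends 2 to 8 months in the control condition after enrolment. For the power figures, linkage is 50% before and 80% after.

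**Formula.** Expected positives = mothers × testing uptake × positivity.

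**Pre-intervention positives**

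- (a) Setting facts. Mothers screened by any method: 612 × 0.02 × 2/12 = 2.0 to 612 × 0.02 × 8/12 = 8.2. Positives: 2.0 × 0.10 = 0.2 to 8.2 × 0.25 = 2.0.
- (b) Planning rates, all mothers: 612 × 0.10 × 0.10 = 6.1 to 612 × 0.20 × 0.25 = 30.6, which is 0.3 to 1.7 per LGA.
- (c) Planning rates, control time only. Control LGA-periods: 5×1 + 5×2 + 4×3 + 4×4 = 43 of 90. Mothers: 43 × 6.8 = 292. Positives: 292 × 0.10 × 0.10 = 2.9 to 292 × 0.20 × 0.25 = 14.6.

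**Post-intervention positives**

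- All mothers: 612 × 0.50 × 0.10 = 30.6 to 612 × 0.60 × 0.25 = 91.8.
- Intervention LGA-periods only (47 × 6.8 = 320 mothers): 320 × 0.50 × 0.10 = 16 to 320 × 0.60 × 0.25 = 48.

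**Precision of a pre-intervention linkage rate near 50%** (exact 95% CI)

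| Linked / positive | 95% CI |
|---|---|
| 3/6 | 12-88% |
| 7/15 | 21-73% |
| 15/31 | 30-67% |

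**Power for 50% against 80% linkage** (normal approximation, two-sided 5%, clustering ignored, so rough and optimistic)

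| Pre vs post positives | Power |
|---|---|
| 3 vs 16 | 22% |
| 6 vs 31 | 36% |
| 15 vs 48 | 62% |
| 31 vs 92 | 88% |

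**Comparability.** The period rates estimate P(linked | tested, positive) in each condition. On the plan's figures the tested fraction moves from 10-20% to 50-60%. The women conditioned on are thus a different selection in each condition, and more positives would narrow the intervals without removing that difference.

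**The case against.** Several points on the other side stand.

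- A reader might infer that the pre-intervention rate cannot be estimated at all. The document does not support that. Its own 10-20% baseline rates imply some 3 to 31 positives, and at the most favourable corner (31 against 92) power for a 30-point difference is 88% with clustering ignored. Imprecise is not inestimable.
- A reader might infer that eligibility removes the women needed. It does not. The 5-year exclusion covers screening before enrolment; an enrolled mother can still be tested during control months. Low background screening is what makes this rare.
- A reader might infer that kits are available only at the event. The document does not say so; it simply describes no other route. The Data analysis sentence also speaks of HPV testing in general, although the Discussion narrows the outcome to self-collection results.
- The verb is to explore. No model, test or effect estimate is promised for linkage, and a table of rates by period would satisfy the sentence. That the result would be reported as an intervention effect is a risk, not a stated plan.
- The Methods paragraph of the Abstract mentions pre-implementation data for each LGA. These could be a source, but the sentence concerns effectiveness and cost, and no linkage data are described.
- A control-period route yielding the planned 10-20% would ease the shortage of positives. It would not make the two groups comparable.

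What survives is the lack of comparability at any count, together with a pre-intervention group that is probably small. The planning rates fit poorly with under 10% coverage, non-routine self-sampling and the exclusion of recently screened mothers, so the low end of the range is more likely.

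**Conclusion.** The concern holds in a limited form. Pre-intervention positives are likely to be very few: about 0 to 2 in the whole trial on the setting facts, or about 3 to 31 if the planning rates are met. Both ranges rest on the assumed 10-25% positivity, and the lower one also on the assumed spread of coverage over 5 years and on 2 to 8 control months. The conclusion that the period contrast is not an intervention effect on linkage needs none of these assumptions. It follows from conditioning on a post-randomisation event that the campaign is designed to make more frequent, and from linkage itself being part of the campaign. This limits one exploratory secondary outcome; the primary analyses and the sample size are untouched.

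**What to change.** Replace the sentence in Data analysis. Report linkage descriptively among HPV-positive mothers in the intervention periods, with the denominator and an LGA-clustered 95% CI, and make no pre/post contrast that is conditional on a positive test. With 31 to 92 positives and about 80% linked (assumed), the exact intervals before allowing for clustering would be about 63-93% (25/31) to 71-88% (74/92), so the descriptive rate is worth having.

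If a randomised comparison is wanted, use all enrolled mothers as the denominator and count those tested, positive and linked. This is defined in both conditions, but it should be labelled as largely a measure of testing uptake. With positivity and linkage equal in the two conditions, it would still rise by a factor of 0.50/0.20 = 2.5 to 0.60/0.10 = 6 on the plan's uptake figures alone.

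The cost is one sentence and no new data. The sponsor gives up an exploratory between-period contrast.
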